**Methods/design:**

This study utilizes a hybrid research design and focuses on examining feasibility, acceptability and preliminary impact, along with factors that influence implementation, to maximize new knowledge. The study combines qualitative methods and a randomized controlled trial, using data to inform and refine protocols and manuals, while testing the preliminary impact of the intervention, compared to best available services (treatment as usual, TAU) at a partnering outpatient mental health clinic (*n* = 60). Contributors to the intervention development research (*n* = 20) are national experts on mental health services, clinic administrators and staff and young adults with direct experience. The intervention involves intensive staff training and 18 months of ongoing service provision, monitoring and supervision. Quantitative survey data will be collected at baseline, 3 months, 6 months, and 9 months measuring mental health and practical life outcomes via self-report measures. Medical records will be used to triangulate self-report data (i.e., primary diagnosis, treatment planning and attendance). Qualitative data focuses on the intervention development process and implementation research and will use constant comparison coding techniques. In this intention-to-treat analysis, we will conduct basic omnibus analyses to examine whether Cornerstone leads to improved outcomes relative to TAU utilizing *t* tests across treatment conditions for each outcome measure specified. We will likewise examine whether changes in the proposed mediating variables differ across groups.

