## Methods

The trial has three aims. Aim 1 is to develop and refine all manuals and protocols for Cornerstone, via individual interviews and feedback meetings with clinic staff and Cornerstone Advisory Council (CAC) members (*n* = 20). Aim 2 will determine the preliminary impact of Cornerstone relative to treatment as usual (TAU) on mediating outcomes (e.g., stigma), and primary outcomes (e.g., service use, mental health, functioning) with a small randomized controlled trial (*n* = 60, 30 per group). Aim 3 will explore influences on implementation through individual interviews with clinic staff and leadership from our advisory team on the changing local, state and national service context (e.g., staffing, training, payment).

This randomized controlled trial utilizes both qualitative and quantitative data to develop and refine Cornerstone, test its feasibility for use across the transition to adulthood within an outpatient mental health clinic, and systematically uncovers factors that could facilitate or impede implementation. The project uses a hybrid model of examining feasibility, acceptability and preliminary impact, alongside implementation, to maximize new knowledge. We know from a feasibility study of youth approaching transition in Detroit that there is promise in the Cornerstone program model, and that it is a complicated proposition to implement a ‘boundary-spanning’ intervention over the transition to adulthood.

This research includes three phases. During phase 1 (months 1–12) we will prepare and set up research offices and databases, convene members of the Cornerstone Advisory Council, develop and modify all manuals and protocols, hire and train project staff, and collect and begin analyzing data for aim 1. In phase 2 (months 12–36) we will conduct the randomized controlled trial of Cornerstone (aim 2), including all trainings, recruitment and enrollment, the intervention (up to 9 months of Cornerstone from baseline to completion), and all data collection (baseline, 3-month, 6-month and 9-month post-tests). Participants in both conditions will be involved for approximately 9 months between baseline and the final follow-up assessment. In phase 3 (months 30–36), we will also conduct a small implementation study. Methods for each phase are described in detail below.

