#### Randomization and sample

The PI utilized a random numbers table to generate the random allocation sequence. The PI has the list of condition by case number and did not share the sequence with any team member. The condition was identified on a sheet of paper within the initial enrollment packet, and all study personnel were trained not to examine the condition before enrolling a transition-age youth and their family.

We will recruit 60 transition-age youth with SMHC and approximately 20 stakeholders. The sample size is typical for the pilot nature of this research. The National Institutes of Health (NIH) grant mechanism under which this proposal was funded (R34) is intended for intervention feasibility and acceptability testing, and therefore we will conduct only exploratory statistical testing of study outcomes. Our primary goal in this proposal is to gather preliminary data regarding feasibility and acceptability of our intervention to inform a future large-scale, fully powered, randomized control trial of Cornerstone. Given the intended pilot nature of this research and our modest sample size, which is due to the logistical constraints of the grant mechanism, conducting formal tests of outcomes or attempting to obtain an estimate of an effect size is not typically recommended. Still, with our sample size of 30 per group we will have 80 % power with *p* = 0.05 to detect a large effect of the intervention (Cohen’s d = 0.73).

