### Interview protocol

#### Timing of assessment and procedures

All participants will be interviewed by the research team at four time points: baseline (beginning of intervention), 3 months, 6 months, and post-test (approximately 9 to 12 months after baseline). The baseline and final interview will last approximately 90 minutes (compensation for participants time is $20/assessment) and the 3-month and 6-month follow-ups will last approximately 60 minutes. The interviews consist mainly of self-report questionnaires with some open-ended questions. The importance of honest responding will be stressed and a measure of social desirability response tendencies will be included for use as a covariate. There is debate about whether interviewer-administered questionnaires yield as truthful responses. If respondents are assured confidentiality, there is evidence to suggest that the differences in the two methods of assessment are minimal (e.g., [45]). Cornerstone participants will complete the assessments in planned meetings at the clinic. Structured and intensive interviewer training for the research staff will be conducted based on a training protocol. We estimate the training to require 8 hours of direct instruction and 4 hours of practice. Interviewer training will cover the following: (a) the research process and the clinic setting, (b) federal law regarding informed consent and the rights of research participants, (c) the basics of interviewing and the specifics of the project interview schedule, (d) coding interviews, (e) managing participant discomfort during and after an interview, (f) education about topics such as the psychosocial effects of poverty, trauma, mental illness and treatment, (g) desensitization to discussing poverty, trauma and mental illness, (h) interviewing participants from diverse cultural backgrounds, and (i) psychiatric interviewing. Then, weekly follow-up research staff meetings will be utilized to reinforce training and provide support throughout the trial.

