Data analysis for aim 2: due to limited sample size we will proceed cautiously to conduct basic omnibus analyses to examine whether Cornerstone leads to improved outcomes relative to TAU, as this study is intended for intervention feasibility and acceptability testing, and therefore we will conduct only exploratory statistical testing of study outcomes. Our primary goal in this proposal is to gather preliminary data to inform a future large-scale, fully powered, randomized control trial of Cornerstone [51]. For each study subject we will calculate the difference, relative to baseline, at the end of the study for each outcome specified (see Table 2 above). A simple *t* test will be used to assess whether these changes differ across treatment conditions. For example, we will examine whether the mean within-person difference between the 9-month assessment and baseline assessment of intention to use services differs for subjects in Cornerstone versus those in TAU. We will likewise examine whether within person changes in the proposed mediating variables differ across intervention groups.

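### The between-arm analysis described in the article is an unadjusted t test on change from baseline: valid, but less precise than adjusting for the baseline score, and with no place for the covariate collected

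*Protocol article*

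**What the plan says.** The Analysis section of the protocol article (aim 2) first defines the analysed quantity: "For each study subject we will calculate the difference, relative to baseline, at the end of the study for each outcome specified". It then says that a simple t "test will be used to assess whether these changes differ across treatment conditions". Within-person changes in the mediators are to be compared across arms likewise. The abstract (Methods/design) agrees, naming t "tests across treatment conditions for each outcome measure specified". The article describes no adjusted or repeated-measures model.

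The section on timing of assessment and procedures says that "a measure of social desirability response tendencies will be included for use as a covariate". It does not say which analysis will use the measure or when it is taken, and Table 2 does not list it.

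The Methods section plans a trial of "60, 30 per group". Randomization and sample states that "with our sample size of 30 per group we will have 80 % power" at the 0.05 level "to detect a large effect of the intervention (Cohen’s d = 0.73"). Enrollment, retention, and tracking expects 55 participants at the end. The outcome testing is called exploratory throughout.

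**The concern.** A change score fixes the coefficient on baseline at 1. Unless the true slope of follow-up on baseline is 1, that is not the best use of the baseline score, and the between-arm comparison carries avoidable noise. With 30 per arm, the chance difference in baseline means has a standard error of sqrt(2/30) = 0.26 SD. Subtracting baseline over-corrects for such a difference when the slope is below 1. Regression estimates the slope from the data.

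What is at stake is the width of the intervals that this pilot passes to the larger trial it is meant to inform. The baseline scores are already being collected, so the precision is available at almost no cost.

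The covariate is a second, smaller matter. Most outcomes are self-reported to an interviewer, and the authors thought response tendency important enough to measure for adjustment. The only test they describe cannot use it.

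**Working it through.** **Inputs from the article.** 30 per arm randomised; 55 analysed (taken as 28 and 27); power 80%; alpha 0.05; d = 0.73.

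**Inputs not in the article.** The correlation r between baseline and 9 months, and the SDs at the two times. I assume equal SDs and show a range of r.

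**The plan's own figure.** Normal approximation: 0.73 × sqrt(30/2) − 1.96 = 0.867, which gives power of 80.7%. The noncentral t gives 79.4%, and d = 0.736 gives exactly 80%. The stated 80% reproduces as a two-sided test with 30 per arm (one-sided would give 87.5%). The article does not say whether the 0.73 is in SDs of the outcome score or of the change score.

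**Variance per participant**, in units of the outcome variance:
- change score: 2(1−r)
- baseline-adjusted: 1−r²
- ratio, adjusted to change: (1−r²) / [2(1−r)] = (1+r)/2
- share of information lost by the change score: 1 − (1+r)/2 = (1−r)/2

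**Does the direction depend on equal variances?** With baseline SD s0 and follow-up SD s1, the change-score variance minus the adjusted variance is s0² + s1² − 2r·s0·s1 − s1²(1−r²) = (s0 − r·s1)². This is never negative and is zero only when the slope r·s1/s0 equals 1. In large samples the adjusted analysis is therefore never less precise. Under equal variances it is more precise for every r below 1.

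**Detectable difference with 55 analysed, 80% power.** The t-test multiplier at 28 and 27 is 0.770 outcome SDs. For the change score, multiply by sqrt[2(1−r)]. For the adjusted analysis, multiply by sqrt[(1−r²)(1 + 1/51)]; the factor 1 + 1/(N−4) charges for estimating the slope.

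| r (assumed) | Information lost, (1−r)/2 | Lost after small-sample charge, N = 55 | Change score (SD) | Adjusted (SD) |
|---|---|---|---|---|
| 0 | 50% | 49.0% | 1.09 | 0.78 |
| 0.3 | 35% | 33.7% | 0.91 | 0.74 |
| 0.5 | 25% | 23.5% | 0.77 | 0.67 |
| 0.7 | 15% | 13.3% | 0.60 | 0.56 |
| 0.9 | 5% | 3.1% | 0.34 | 0.34 |

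For example, at r = 0.5 the change score gives 0.770 × sqrt(1.0) = 0.77. The adjusted analysis gives 0.770 × sqrt(0.75 × 1.0196) = 0.67.

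At r = 0.5, before the small-sample charge, 60 participants analysed by change score carry the information of 60 × 0.75 = 45 analysed with adjustment.

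**Where the gain runs out.** With the small-sample charge, the two methods break even when (1+r)/2 × 52/51 = 1, at r of about 0.96.

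**The case against.** The strongest reply is that this is an exploratory pilot. The article makes feasibility and acceptability the primary goal, says that formal outcome tests are not usually advised at this size, and gives the small sample as its reason for keeping the analysis basic. No confirmatory decision rests on the t test. That lowers the stakes. It does not make the less precise method preferable: one covariate costs one degree of freedom, and a small sample is where precision is most useful.

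Four stronger readings are tempting, and the documents do not support them.

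- **A reader might take 15% to 35% as the actual loss.** It holds only for r from 0.7 to 0.3 with equal variances, and the article gives neither. It also concerns only roughly continuous scales, not items such as insurance, residence or attendance.
- **A reader might infer that the change-score test is biased.** Under randomisation the difference in mean change is unbiased. The error from a chance baseline imbalance is conditional on that imbalance and is already counted in the variance, so it is not a second defect.
- **A reader might see a flat contradiction over social desirability.** The article does not tie that covariate to the t test, and a fuller plan not shown here may use it elsewhere. What stands is that the one between-arm test described cannot take it.
- **A reader might compare the adjusted 0.74 SD at r = 0.3 with the stated d = 0.73.** The closeness is a coincidence, because the article does not say which SD its d refers to.

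**Conclusion.** The point holds as one of precision, not validity. The only between-arm analysis this article describes is an unadjusted t test on change, and baseline-adjusted regression on the same data would be more precise for any correlation likely to matter here. The size depends on an unstated r: about a quarter of the information at r = 0.5, with the detectable difference at 55 analysed falling from 0.77 to 0.67 SD, and less at higher correlations. These figures assume equal variances at the two times and 55 participants with both scores. They allow for estimating the baseline slope but not for a second covariate. The unused social desirability measure is a lesser point, a gap between two sections of the article. The change is worth making because it costs almost nothing, even though the testing is exploratory.

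**What to change.** In the Analysis section (aim 2) and the abstract, replace the t test on change for the continuous scales measured at baseline: stigma, mistrust, efficacy, intention, recovery, CES-D and perceived stress. Specify a linear regression of the 9-month score on arm and baseline score, reporting the adjusted mean difference with its 95% CI.

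State when social desirability is measured. If there is a baseline score, add it as a covariate. If it is measured only after randomisation, leave it out of this model, since arm may affect it. In either case, say in the Analysis section where it is used.

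The change-score t test may stay as a sensitivity analysis.

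The cost is a few sentences and one degree of freedom, or two if social desirability enters. The baseline-adjusted model needs no new data, visits or participants. The article reports 30 of the planned 60 enrolled, so the change could be fixed in writing before the outcome data are complete.

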### Ethical issues and dissemination

The RCT protocol for all research aims has been reviewed and approved by the New York University Committee on Activities Involving Human Subjects as of November 30^,^ 2016 (IRB-FY2016-172). For protocol modifications the research team will submit an amendment to the Committee on Activities Involving Human Subjects. Consent (and assent for those under 18) to enroll in the study will be processed and obtained by the PI or trained project research staff who have all been trained on activities involving human subjects.

## Discussion

Given the lack of mental health service engagement among transition-age youth and young adults and the toll that untreated mental illness can take on individuals, families and society, an intervention designed to address both mental health and functional outcomes is sorely needed. This research has the potential to contribute to the understanding of how to decrease the number of young adults with unmet mental health needs, by focusing on the transition to adulthood with innovative service delivery strategies that span development. This can be done by partnering with professionals who work across systems, including the state office of mental health and leading implementation scientists. The testing of this intervention is timely given the changes in the public and private insurance system(s) through the Affordable Care Act and New York State Medicaid Redesign, both of which are likely to result in more young adults having access to much-needed health insurance, which will pave the way for increased access to mental health services.

## Trial status

All hiring and training of experimental site personnel and research staff have been completed. We have recruited and enrolled 30 participants for aim 2 of the Cornerstone trial.

## Abbreviations

ACA: Affordable Care Act
BSCM: Boundary-spanning case manager
CAC: Cornerstone Advisory Council
CTI: Critical Time Intervention
ID: Identification number
PI: Principal investigator
RCT: Randomized controlled trial
RRM: Recovery role model
SMHC: Serious mental health condition
TAU: Treatment as usual
TAY: Transition-age youth
TF: Transition facilitator
TIP: Transition to Independence Process Model
